
### **Specific aspects of the treatment registry**

Participation to this treatment registry of CL/MCL will be proposed by the ITM team in priority to the main established university-based travel clinics and dermatology practices in Belgium, as suspected cases are soon or late referred to these facilities for the specialized diagnostic workup and therapeutic decisions. However, the number of cases seen in Belgium remains low.

According to a retrospective study conducted at the ITM in Antwerp between 2010 and 2018, only 147 cases of CL/MCL were identified, averaging fewer than 20 cases per year. Despite a modest increase in diagnoses over time, to ensure a sufficient and representative inclusion of cases across different *Leishmania* species, the registry will be progressively opened to other European travel clinics affiliated

with TropNet or the *LeishMan* network to allow rapidly increasing the number of inclusions and obtain some conclusive sample size for the different species.

Like for the other tropical conditions which will be targeted by Tropistry, the REDCap-based CRF for CL and MCL will be tailored to capture the many and rather complex specificities of management. Sections will be specifically designed to assess the epidemiological risks, quality of diagnosis and robustness of monitoring as well as to appropriately evaluate the final clinical outcome. The list of data which will be collected during the study is available in Annex 4.

As previously explained, Tropistry will not only be a unidirectional data collection tool, but also a platform to promote in return the best clinical practice, based on the limited available evidence or local experience. Instructions for management will be suggested by the ITM team and other experts, through short texts appearing at the beginning of each section (for diagnosis, treatment, and follow-up). Also, a panel of ITM experts could be reached at any moment via secure mail ([contact]), to discuss any difficult decision.

These “recommendations” will of course evolve with the scientific advances and new knowledge (included that generated by Tropistry). It is important to highlight that each center may propose different therapeutic regimens, according to local/national guidelines. The decision for the type of treatment of CL should mainly rely on (1) the *Leishmania* species, (2) the clinical aspects of the lesions, (3) the host immunity and local drug availability and experience. A new classification of CL is emerging in international literature, with the distinction between “simple CL” and “complex CL”, although there are still some slight discrepancies between groups of experts. To address these discrepancies, we follow the approach used by Vandeputte et al. in a recent retrospective study about leishmaniasis management in Belgium^10 adapting the classifications proposed by the IDSA and the *LeishMan* group to ensure that all cases could be consistently categorized as either simple or complex. As noted in that study, the two guidelines present certain gaps and are not fully congruent; therefore, for study purposes, an adapted classification was applied to overcome these inconsistencies and allow for standardized case assignment (see next table).

**Definition of complex cutaneous leishmaniasis according to IDSA, the LeishMan group and the one proposed by Vandeputte et al.**

| Criteria                   | IDSA 7a                                          | LeishMan group               | Vandeputte et al.                   |
|----------------------------|-------------------------------------------------------------|-------------------------------------------------|--------------------------------------------------|
| Size                       | >4 cm                                                       | >3 cm                                           | >4 cm                                            |
| Number of lesions          | >4                                                          | >3 or >1 b                           | >4                                               |
| Location                   | Face, ears, eyelids, lips, fingers, toes, joints, genitalia | “Delicate location”/ ‘cosmetically disfiguring’ | Ears, eyelids, nose, lips, joints, fingers, toes |
| Mucosal involvement        | Yes                                                         | Yes                                             | Yes                                              |
| Immunosuppression          | Yes                                                         | Yes                                             | Yes                                              |
| Failure to local treatment | Yes                                                         | Yes                                             | Yes                                              |
| DCL/LR                     | Yes                                                         | Unclear                                         | Yes                                              |

|                      |         |         |         |
|----------------------|---------|---------|---------|
| Subcutaneous nodules | Yes     | Unclear | Yes     |
| Lymphatic spread     | Yes     | Yes     | Yes     |
| Infection in Bolivia | Unclear | Yes     | Unclear |

DCL: diffuse cutaneous leishmaniasis, LR: Leishmania recidivans

aFor the IDSA guidelines there are cases where the simple and complex is not mutually exclusive; e.g. 1-4 cm size, and 2-4 lesions

bA distinction is made between Old-World species (with the addition of *L. mexicana* from the New-World), for which more than 3 lesions are considered to be complex, while for New-World species (with the exception of *L. mexicana*) having multiple lesions is sufficient to qualify as complex cutaneous leishmaniasis.

In general, for simple CL, observation/simple wound care or local treatment are sufficient, while systemic therapy should be considered for complex CL. Of note there are still slight differences between guidelines about some criteria (especially regarding the size and number of lesions) but treatment decisions based on "common sense" will be suggested whenever discrepancies occur. In all cases, confirmation of the diagnosis is important, and whenever feasible, PCR-based species identification will be recommended because it increasingly guides therapy choices. However, species typing might not be available everywhere; in such cases, clinical judgment and knowledge of the probable region of infection will guide management.

Follow-up, treatment failure, and scarring assessment have been standardized in the registry following recent international recommendations. Clinical response is now evaluated at predefined time points: Day 42 and Day 90 (initial cure assessments), 6 months (final cure), and optionally at 9–12 months to detect relapse (see Figure). Treatment failure is defined as <50% re-epithelialization or flattening by Day 42, or <100% re-epithelialization or flattening by Day 90, in line with the consensus reached in harmonized clinical trial methodologies for cutaneous leishmaniasis. In addition, scar outcomes are systematically assessed using a standardized grading (from no visible scar to severe disfigurement or functional limitation) and classified by type (e.g. flat, atrophic, hypertrophic, keloid, pigmentary alteration). This approach enhances comparability across sites and aligns with WHO/TDR and DNDi guidance for clinical evaluation of CL.

[figure not shown]

Based on Olliaro P et al. Harmonized clinical trial methodologies for localized cutaneous leishmaniasis and potential for extensive network with capacities for clinical evaluation. PLoS Negl Trop Dis 2018 12(1): e0006141.

As already highlighted, the purpose is to make Tropistry as accessible as possible for busy clinicians confronted with any of the target diseases. For pragmatic reasons, inclusion and data entry will be retrospective (with reasonable delay of maximum 6 months after initial diagnosis), and considered as secondary use of clinical data for institutions where an optout strategy is in place. In other settings, a formal written informed consent will be requested for each included patient.

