| Register Duration   | 
Registry start date: 10/2024
 
Registry end date: none
                                                                                                                                                                                                                                                                                                                                                                                                                                                                                                                                                                                                                                                                                                                                                                                                                                                                                                                                                          |
| Statistical Methods | 
The REDCap database will be analyzed on annual basis to statistically describe different variables as patient demographics, baseline clinical presentation, methods of diagnosis, staging of disease, (recommended) treatments, frequency and pattern of adverse events, complications and clinical outcome. Deviations with suggested treatments will also be captured (as well as reasons for alternative decisions). Association between specific treatment strategies and patient safety/clinical effectiveness will be analyzed using analysis of variance or Student's t-test for the continuous variables (or equivalent non-parametric tests for non-normally distributed variables Mann–Whitney U test or Kruskal-Wallis test) and the chi-square tests or Fisher's exact test for the categorical variables as well as multivariable regressions. Time to event analysis, by using Kaplan-Meier and Cox proportional hazard models will be performed to examine factors associated with specific outcomes.
 |

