## 4. OBJECTIVES

### 4.1. PRIMARY OBJECTIVE

To document the **safety** (frequency and pattern of adverse events) and **clinical effectiveness** (cure or stabilization rate at relevant timepoint) of current treatments for patients diagnosed with any of the selected tropical diseases (listed below\*) in Belgian and European hospitals and travel clinics.

1. Acute schistosomiasis
2. Neurocysticercosis
3. Chagas disease
4. Cystic echinococcosis
5. Cutaneous leishmaniasis

\*This selection is indicative and limited to parasitic diseases, based on the considerations described in the text, and may evolve according to the needs. Also, the extension of the registry to each disease will be progressively phased, following the proposed order.

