#### C. Documentation of clinical course and outcome

- To document the (successive) antimicrobial and adjunctive treatments administered and reasons for any interruption or change
- To observe whether the treatments are administered according to the supervised ITM's state-of-the-art and document the reasons for deviation
- To document the follow-up strategy in the real-life (frequency of visits, monitoring...)
- To determine the proportion of documented microbiological cure, in addition to the defined clinical cure (or stabilization/non-progression)

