## 5.5.VARIABLES AND EPIDEMIOLOGICAL MEASUREMENTS

Documentation of data at ITM will be pseudonymized, so that missing information could be retrieved by request to the treating physician.

The core “generic” dataset for all selected diseases includes baseline patient characteristics, details on care-seeking trajectories, clinical findings at presentation, diagnostic methods and ascertainment, information on staging, and recommended / administered treatments normally during the whole follow-up period and final clinical/microbiological outcome whenever possible. CRF will be tailored to each specific disease, as the diagnosis and treatment may differ a lot. Due to potential evolving scientific research questions, adjustments of the register/template/dataset might be necessary throughout the study period, in particular if new target disease is identified or new treatments enter clinical practice. Minor adjustments will be collected and notified to the ethics committees; substantial changes will be submitted via an amendment.

The collected data will generically include the following core parameters after anonymization. A disease-specific CRF will be however each time elaborated as all target diseases have important clinical, diagnostic, and therapeutic specificities.

- **General Setup**
  - Epidemiological data on the case: principal investigators name, country, institution, level of care of the institution (e.g., primary care, secondary care)
  - Details on the entered case: Documentation in any other registry (yes/no, if yes DOI), case already published (yes/no)
- **Patient demographics and clinical features at time of diagnosis and initial treatment**
  - Age group, gender, height, weight, associated infections, relevant comorbidities, using Charlson Comorbidity Index (CCI) and in particular immunosuppressive conditions and/or treatments
  - Pre-diagnosis trajectory
  - Clinical signs and symptoms of infection leading to diagnosis and treatment
  - Relevant laboratory parameters (CRP, eosinophilia...)
- **Details on the diagnostic method / case ascertainment**
  - Correspondence to pre-specified case definitions (as composite references standards are often needed for parasitic diseases)
  - Information on disease staging when relevant
  - Details on direct microbiological diagnosis (whenever available)
- **Initial and second line (if any) treatment and outcome**
  - Recommended treatment (in the state-of-the-art section or national guidelines)

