  - Administered antiparasitic and adjunctive treatment (in case different of recommended, request to explain the reason for deviation)
  - Description and timing of drug-related adverse event if any

- Need of treatment interruption and reason (availability, adverse event, disease progression...)
- Laboratory changes (Electrolytes, Creatinine, liver function panel, Platelet count, red blood cell count, hemoglobin, white blood cell count, neutrophils, leukocytes, eosinophil count)
- Frequency and timing of follow-up visits with specific findings, if any
- Treatment response regarding clinical features (disease progression vs. stabilization vs. cure), with day of assessment
- Treatment response regarding microbiological outcome: eradication, reduction of the parasitic load, with day of assessment
- If inpatient stay: days on normal ward, intermediate care, intensive care unit total, as a marker of morbidity
- In case of death, cause of death
- Additional information on the case can be entered as a narrative

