Cutaneous leishmaniasis can be managed with either local or systemic therapy, depending on the clinical presentation and the infecting species. Local therapies used for simple CL may consist of intralesional pentavalent antimonials, cryotherapy, topical paromomycin and local heat therapy. For simple CL due to species like *L. major* or *L. mexicana*, local therapy is often sufficient. Patients should be monitored for response; if lesions do not show healing within a few months, escalation to systemic therapy might be needed. The main systemic therapies used for complex or refractory CL, and for MCL usually consist of pentavalent antimonials (meglumine antimoniate or sodium stibogluconate), oral miltefosine and liposomal amphotericin B. Other systemic options are: pentamidine isethionate, azole antifungals (see Annex 3 for detailed general and specific treatment by etiological species based on the *LeishMan* group guidelines). However, treatment of CL/MCL remains controversial and heterogeneous. Over the past decades, several national and international expert groups (e.g. *LeishMan* consortium in Europe, IDSA/ASTMH in North America) have published therapeutic guidelines for leishmaniasis in travelers . While these guidelines are aligned on many points, they also show discrepancies because evidence for optimal treatment is limited – many recommendations are based on small case series, often in endemic areas with immune populations, or expert opinion rather than robust clinical trials. As a result, clinical practice varies greatly between centers and countries. For instance, whether to treat certain Old World CL cases with local therapy or systemic therapy can differ by guideline, and approaches to New World CL to prevent (late) mucosal spread are not uniform. This is further complexified by the increasing recognition that species matters in terms of treatment response. This paucity of data and heterogeneous use of species diagnosis lead to uncertainty about which treatments achieve the best outcomes for the large variety of clinical scenarios. In addition, some therapies (e.g. antimonials) may have significant toxicity while the success rate of newer or repurposed compounds appears highly variable and setting-dependent. For example, a recent European retrospective analysis found that pentavalent antimonial therapy yielded about a 76% cure rate overall (with higher success when given intralesionally), whereas liposomal amphotericin B (the emerging standard of care because of its safety) had only ~44% cure rate in *L. tropica* infections , highlighting the need to better understand which treatments work for which species.

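### The cutaneous leishmaniasis failure rule looks only at the lesion, so a patient who heals after an unplanned change of treatment is not a failure

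*Protocol*

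**What the plan says.** The follow-up text of Protocol section 9 (Specific aspects of the treatment registry) presents failure as standardized: "Treatment failure is defined as <50% re-epithelialization or flattening by Day 42, or <100% re-epithelialization or flattening by Day 90". Response is assessed at Day 42, at Day 90 and at 6 months (final cure), with an optional later visit for relapse.

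This outcome serves the primary objective in section 4.1, where effectiveness is the "cure or stabilization rate at relevant timepoint" of current treatments. It also serves the analysis in the Protocol Summary: "Association between specific treatment strategies and patient safety/clinical effectiveness will be analyzed".

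Changes of treatment are expected and recorded:
- The CL background says of simple disease treated locally that "if lesions do not show healing within a few months, escalation to systemic therapy might be needed".
- Section 4.2 C documents the successive "antimicrobial and adjunctive treatments administered and reasons for any interruption or change".
- The core dataset in section 5.5 has a block headed "Initial and second line (if any) treatment and outcome" and an item "Need of treatment interruption and reason (availability, adverse event, disease progression" and so on.

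None of these places says how a change of treatment bears on the failure rule.

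**The concern.** A treatment registry has to attribute healing to the treatment that produced it. Section 9 gives this purpose for CL itself, since it wants to know which treatments work for which species. A rule that reads only the lesion cannot tell healing on the first drug from healing after a second one was started.

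If results are tabulated by initial treatment, a patient switched early who then heals on time counts as a success of the drug that was abandoned. Measured against cure without any other anti-leishmanial treatment, this error has one direction: the first treatment's apparent cure rate can rise but not fall.

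**Working it through.** The Protocol states no figure on this point, so there is none to reproduce. The check applies the written rule to the possible patient histories and compares the result with a rule that also counts an unplanned switch.

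| History | Day 42 | Day 90 | Class as written | Class for the initial treatment if a switch counts |
|---|---|---|---|---|
| A. No switch | at least 50% | 100% | not a failure | cured |
| B. Unplanned switch | below 50% | any | failure | not cured |
| C. Unplanned switch | at least 50% | below 100% | failure | not cured |
| D. Unplanned switch before Day 90 | at least 50% | 100% | **not a failure** | **not cured** |
| E. Healed at Day 90 without a switch, re-treated before 6 months | at least 50% | 100% | not a failure | cured at Day 90, not cured at 6 months |

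1. **Where the rules differ.** Rows A to C are classed alike. The rules part in row D and, at the 6-month assessment only, in row E. A lesion unhealed at Day 90 has already failed, so at 6 months the switch matters only for patients who were fully healed at Day 90.

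2. **Who can be in row D.** The change must come early enough, or the lesion must be healing well enough, for both thresholds to be met. A drug stopped for intolerance or lack of supply before Day 42 fits. Escalation for poor response mostly does not: the background places it after some months without healing, when most such lesions have failed at Day 42 or Day 90. The group is therefore narrow.

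3. **Whether another section closes the gap.** Sections 4.2 C and 5.5 record treatment lines, changes and reasons but do not tie them to failure. The section 9 table lists failure of local treatment as a criterion for complex CL; that classifies disease and is not an outcome rule.

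4. **Direction and size.** Let p be the percentage cured on the initial treatment alone, and e the share of the remaining patients who end in row D. The lesion-only rate credited to the initial treatment is p + (100 − p) × e, so the excess is (100 − p) × e. This is never negative, and it is zero if nobody is in row D. The documents give no switch rate and so no value of e. The direction follows from the rule; the size cannot be computed.

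**The case against.** **The harm needs a condition that the Protocol does not state.** A reader might infer that the registry will misattribute healing. The documents do not support that. The Summary speaks of treatment strategies and section 4.1 of current treatments. Section 5.5 collects outcome for initial and second-line treatment, so analysis by treatment line is possible. This objection stands and makes the point conditional.

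**Attribution after a switch belongs in a statistical analysis plan.** One may exist. But the failure definition is fixed in the Protocol, and the class it gives in row D follows from its wording. The follow-up figure and Annex 4 are not shown and might bear on this, which limits confidence.

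**The rule follows a cited consensus and serves comparability.** That is a fair reason to keep the lesion-only result. It is no reason against a second result that answers a different question.

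**Counting every switch as non-cure has its own bias.** A patient who is healing well and changes drug because of supply or an adverse event might have healed anyway. This also stands, and it is why the reasons should be separated and tested in a sensitivity analysis.

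**A large bias might be inferred from the cure rates in the background.** There, "pentavalent antimonial therapy yielded about a 76% cure rate overall", against about 44% for liposomal amphotericin B in one species. These rates come from different patient groups and say nothing about how many patients switch and still heal on time. They cannot be turned into a size.

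**Conclusion.** The point holds in a limited form. As written, the CL failure rule classes a patient in row D as a non-failure, and no text shown corrects this. If effectiveness is reported by initial treatment, the first drug receives credit for healing that followed another treatment.

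The size is unknown and probably small, and no numerical claim is justified. The conclusion rests on the section 9 text as the full definition and on reporting by initial treatment. A reader might infer that the Protocol ignores second-line treatment or that its lesion thresholds are wrong; neither is supported. The thresholds can stand as a measure of lesion response. What is missing is the link between that response and the treatment line. This is an inexpensive improvement, not a serious flaw.

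**What to change.** In section 9, keep the present definition and add, for the effectiveness of the initial treatment:

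- The start of any other anti-leishmanial treatment, local or systemic, that was not planned at the outset and begins before the Day 42, Day 90 or 6-month assessment counts as not cured on initial treatment at that assessment.
- A combination or sequence planned at the start is one treatment.
- Switches for lack of response or progression are reported separately from those for intolerance or availability. In a sensitivity analysis only the former count as failure, and the others are judged by the lesion criteria.
- The lesion-only result, as now defined, is reported alongside for comparability.

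The cost is one clause and one derived variable. No new core data item is needed, because sections 4.2 C and 5.5 already cover treatment lines, changes and reasons. The CL form in Annex 4 should be checked to confirm that it captures when the second treatment started and whether it was planned. The downside is slightly lower first-line cure rates and one element beyond the cited consensus wording.
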